**Fig. 2 Fig2:**
[figure not shown]
Algorithm to continue or discontinue daily exoskeleton training

#### Usual care intervention (control)

Participants randomized to the Usual Care group will receive standard physical therapy care during their rehabilitation stay. Standard of care differs between sites, but typically involves 30–60 min physical therapy sessions, 4–5 days a week. No specific instructions will be given to therapists providing therapy in the Usual Care group, except that they cannot use the robotic exoskeleton. Generally, physical therapy during stroke rehabilitation is provided with patient-specific goals in mind, and typically places a large focus on mobility and gait training. Participants in both the Exoskeleton and Usual Care group will be monitored twice a week using an activity tracker (activPAL3 micro, PAL Technologies, Glasgow, UK) to observe the amount of upright standing and walking performed in the physical therapy sessions per group.

#### Evaluations

All participants will be assessed at recruitment (baseline), at discharge or after 8 weeks of the intervention, and at 6 months by an assessor who is blind to group allocation. The exoskeleton intervention will be discontinued after 8 weeks, and standard physical therapy will be provided to all participants beyond 8 weeks for whom it is deemed appropriate by their care team.

#### Primary outcome

The primary outcome will be walking ability, measured using the Functional Ambulation Category (FAC) [29]. This is a 6-item scale designed to classify the level of physical support required by subjects in order to walk safely over 10 ft, extending from 1 (unable to walk without the assistance of two people) to 6 (independent walking overground on uneven surfaces and on stairs). It has been shown to have good test-retest reliability and validity in the hemiparetic stroke population [30]. The FAC is also responsive to change within the first four weeks post-stroke and up to six months post-stroke [30]; unlike other walking measures of speed or distance, a value is assigned for the FAC even if the participant is not yet independent in walking.

#### Secondary outcomes

The secondary outcome measures will assess stroke impairment, walking performance (speed, endurance, daily step count), balance, cognition, and quality of life. The secondary outcome measures and schedule of data collection are listed in Table 2.

**Table 2 Tab2:** Schedule of data collection

Study Procedures	Screening	Baseline evaluation	Post-intervention evaluation	Six-month evaluation
Timepoint	-T_1_	T_0_	T_1_	T_2_
Informed consent	+			
Inclusion/exclusion criteria	+			
Demographics		+		
Randomization		+		
Primary outcome measure				
Functional Ambulation Category [30]		+	+	+
Secondary outcome measures				
*Impairment*				
Fugl-Meyer Assessment (Lower extremity) [31]		+	+	+
*Functional*				
5-Meter Walk test [32]			(+)	(+)
6-Minute Walk test [33]			(+)	(+)
Berg Balance Scale [34]		+	+	+
activPAL mean step count (in PT)			+^a^	
Days to unassisted ambulation			+^a^	
activPAL daily step count over 4 days [35, 36]				+
*Cognitive*				
Montreal Cognitive Assessment [37]		+	+	+
*Quality of life*				
Patient Health Questionnaire [38]		+	+	+
36-Item Short Form Survey [39]		+	+	+
Adverse events screen			+^a^	+

PT: Physical therapy.

() Parentheses indicate that the outcome will be assessed if the participant is able to walk without physical assistance.

^a^indicates that the measure will be taken or monitored throughout the intervention period

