#### Exoskeleton device

The EksoGT powered robotic exoskeleton (Ekso Bionics, Richmond, California, USA) will be used to provide the experimental intervention for this study. This exoskeleton has bilateral motor-actuated joints at the hip and knee, as well as a spring-loaded articulation at the ankle to support toe-off and foot clearance during gait via a footplate. The EksoGT is able to power the user’s lower limbs in a walking pattern autonomously (without any active participation by the user), as well as with varied assistance to accommodate any force contribution by the user. The device software allows the therapist to control the degree of assistance, the parameters of gait (step height, step length, swing speed, etc.) and the automaticity of walking (how each step is triggered). These settings can be programmed to tailor the gait training to the individual to ensure active participation that is appropriately challenging. Guidelines for programming the device software to progress gait training with respect to robotic assistance are available in Additional file 1. The device does not provide balance support, and so the user is responsible for maintaining balance and shifting their weight appropriately.

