#### Exoskeleton intervention (experimental)

Participants in the Exoskeleton group will have 75% of their standard physical therapy sessions replaced with exoskeleton-based gait rehabilitation. For example, 3 out of 4 weekly physical therapy sessions, or 45 min out of every 60-min session, will be dedicated to the exoskeleton intervention, reserving 25% of therapy time to be dedicated towards other goals. Participants in the Exoskeleton group will wear a powered robotic exoskeleton for their physical therapy sessions beginning after the baseline assessment to allow for repetitious stepping and walking practice from early in their rehabilitation stay. Training will be safely progressed, as tolerated, to reduce the amount of assistance provided by the exoskeleton and to increase the duration of continuous walking bouts. Guidelines for training progression can be seen in Table 1, and specific device programming is available in Additional file 1.

**Table 1 Tab1:** Training progression for experimental group receiving exoskeleton intervention

Timing	Exoskeleton training guidelines
Week 1 (i.e. First 3–4 exoskeleton sessions)	- Require 30 min of upright time in exoskeleton, no set requirement for time in walking (expect approximately 10 min) - Aim for at least 250 steps per session - Familiarize with device, high assistance from therapist and robotics
Week 2 (i.e. 5th session and on)	- Require 15 min of walking time, of 30 min of upright time - Aim for 400 steps per session - Begin reducing assistance from therapist and robotics
Week 3 (i.e. 10th session and on)	- Require 20 min of walking time, of 30 min of upright time - Aim for 550 steps per session - Continue reducing assistance from therapist and robotics
Week 4 and beyond (i.e. beyond 15 sessions)	- Require 25 min of walking time, of 30 min of upright time - Aim for 700+ steps per session - Minimal assistance from therapist and robotics

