#### Statistical analyses

Descriptive statistics will be used to summarize data. An analysis of covariance (ANCOVA) will be performed to detect post-intervention differences between groups for the primary and secondary measures, using the respective baseline score as the covariate [41]. The significance level will be set at 0.05, and all statistical tests will be two-tailed. Participant data will be analyzed on an intention-to-treat basis, and any missing data will be assessed and analyzed as appropriate using multiple imputation [42]. For measures without a baseline score (i.e., 5-Metre Walk Test, 6-Minute Walk Test), an analysis of variance (ANOVA) will be employed. Confidence intervals (95% CIs) will be reported, where applicable.

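### Step count during therapy is classed as a functional secondary outcome, but it mixes delivered treatment dose with recovery and should be reported descriptively

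*Protocol article*

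**What the plan says.** Table 2 (Secondary outcomes) places "activPAL mean step count (in PT") in the secondary outcome block, under the functional sub-heading. It has no baseline entry, and its footnote "indicates that the measure will be taken or monitored throughout the intervention period".

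The Statistical analyses section plans comparisons between groups "for the primary and secondary measures", two-tailed at 0.05, with ANOVA where a measure has no baseline score. No sentence exempts the in-therapy count.

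Three other places bear on what the count measures:

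- Exoskeleton device: the device can move the legs "in a walking pattern autonomously (without any active participation by the user"), and can also work with variable assistance.
- Exoskeleton intervention, Table 1: the first week carries the instruction "Aim for at least 250 steps per session". The targets then rise to 400, 550 and 700 or more, and 75% of this arm's therapy is given over to the exoskeleton programme.
- Usual care intervention: therapists receive no instruction except not to use the device. The tracker is worn in both arms "to observe the amount of upright standing and walking performed in the physical therapy sessions per group".

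The prose introducing the secondary outcomes names "walking performance (speed, endurance, daily step count") and does not mention steps taken in therapy. A separate daily count over four days is scheduled at six months.

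**The concern.** An efficacy outcome should show what the treatment did for the patient. Steps taken during physical therapy are largely part of the treatment: the protocol randomises how that therapy time is spent, and in one arm only it supplies a stepping device and sets step targets. A comparison of the two arms then partly asks whether the programme was delivered as planned.

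Coming off the device does not remove the imbalance. A participant whose therapist stops using the exoskeleton must still spend 75% of weekly therapy time on gait retraining, a requirement that usual care does not have.

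The protocol hypothesises greater improvement in function, and its Discussion says the results will guide clinicians on whether to use such devices and for which outcomes. With the count labelled functional and tested at 0.05, a difference in dose could be cited as a functional gain.

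**Working it through.** **Classification.** The Usual care section gives the in-therapy tracker an observational purpose, the amount of standing and walking in each group. The Secondary outcomes prose names only daily step count. Table 2 alone makes the in-therapy count a functional outcome, and the general analysis rule then brings it under a between-group test. As a secondary measure without a baseline, it would fall under ANOVA.

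**Size of a dose-only difference.** The plan gives no expected value, SD or power for this measure, so there is no figure of its own to reproduce. The following is an illustration with zero effect on recovery.

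Inputs from the protocol:
- 20 participants per arm and two-sided alpha 0.05.
- Table 1 targets, read as 250 for sessions 1–4, 400 for sessions 5–9, 550 for sessions 10–15 and 700 from session 16.
- The protocol's own example of three device sessions out of four per week. Over the eight-week maximum this gives 3 × 8 = 24 exoskeleton sessions; over four weeks it gives 3 × 4 = 12.

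Assumptions, because the protocol gives no figure:
- Usual-care average U of 100 to 400 steps per session.
- Between-participant SD of 150 to 300 steps.
- Targets just met, usual-care volume in the fourth session, and monitored sessions typical of all sessions.

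Mean target M per exoskeleton session:
- 24 sessions: (4×250 + 5×400 + 6×550 + 9×700)/24 = 12,600/24 = 525.
- 12 sessions: (4×250 + 5×400 + 3×550)/12 = 4,650/12 = 387.5.

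Built-in gap = (0.75M + 0.25U) − U = 0.75(M − U). The chance of p<0.05 is the power of a two-sample t-test with standardised difference gap/SD and 20 per arm.

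| Sessions | U | Gap (steps) | Chance, SD 150 | Chance, SD 300 |
|---|---|---|---|---|
| 24 | 100 | 319 | 100% | 91% |
| 24 | 200 | 244 | 99.9% | 71% |
| 24 | 300 | 169 | 93% | 41% |
| 24 | 400 | 94 | 49% | 16% |
| 12 | 100 | 216 | 99% | 60% |
| 12 | 200 | 141 | 82% | 30% |
| 12 | 300 | 66 | 27% | 10% |
| 12 | 400 | −9 | 5% | 5% |

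The last row is the nominal error rate: there the artefact is gone.

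The protocol's other example gives 45 of every 60 minutes to the device. If the full target is met in each session and a quarter of usual-care volume is added, the gap is M + 0.25U − U = M − 0.75U, which is larger. At U = 400 it is 525 − 300 = 225 steps over 24 sessions (64% to 99.6%) and 387.5 − 300 = 87.5 steps over 12 sessions (15% to 44%).

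The result depends mainly on U. The Background says that walking practice in rehabilitation is especially low in patients who need more help from their therapist, and such patients are the ones enrolled. That points to the upper rows of each block, but it supplies no number.

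**The case against.** Several points on the other side have force.

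- The test is inferred. The ANOVA sentence names only the two walk tests, the ANCOVA sentence speaks of differences after the intervention, and this count accumulates during it. Table 2 is a collection schedule, and its last block also holds the adverse events screen. Even so, the row stands under the secondary outcome heading and the analysis rule covers secondary measures without exception, so as written the test applies.
- The protocol already states a descriptive purpose for the tracker. This is true, and it is why the fix is small; it does not undo the classification in Table 2.
- Whether the device increases walking practice is a fair question. It is, but it concerns delivery of treatment, and a description by arm answers it.

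A reader might go further and infer that the steps are made wholly by the robot, so that the count contains no recovery at all. The documents do not support that. Assistance is variable and meant to be reduced, the user must keep balance, and the highest target is paired with minimal assistance from therapist and device. The count is a mixture.

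A reader might also infer that a significant result is nearly certain, for instance because a gap of one SD gives 87% power with 20 per arm. That figure assumes the gap it needs. The protocol gives neither a usual-care count nor an SD, the targets of one arm are not a difference between arms, and usual care is itself said to give much attention to mobility and gait. The range in the table is what can be defended.

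Nor do the documents say that the count will be presented as a functional advantage. The labelling allows it; nothing announces it.

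**Conclusion.** The point stands in a limited form. Table 2 and the analysis rule together make a measure that mixes dose and recovery into a tested functional outcome, at odds with the tracker's stated purpose and with the prose on secondary outcomes. A between-arm difference in this count cannot be read as functional benefit, whatever its size.

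A significant difference without therapeutic effect is likely if usual-care counts are low, but it is not assured. With three of four sessions in the device, the chance is about 16% to 100% over 24 sessions and about 5% to 99% over 12. These figures rest on the assumed usual-care counts and SDs and on the targets being just met. The classification problem does not depend on them.

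The Functional Ambulation Category, which is the primary outcome, and the daily step count at six months, scheduled after exoskeleton training has ended, are unaffected.

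**What to change.** Move the in-therapy activPAL count out of the secondary efficacy outcomes in Table 2 and list it as a measure of treatment dose or fidelity. Report it by arm with means and confidence intervals and no efficacy test, in line with the purpose given in the Usual care section, and say in the Statistical analyses section that the secondary comparisons do not include it. Keep the 4-day daily count at six months as the step-count outcome.

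The data collected stay the same. The cost is a change of wording and one fewer tested secondary measure.

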## Background

Stroke is a leading cause of adult disability, often resulting in hemiparesis, altered sensation, incoordination, cognitive changes, and speech disturbances [1, 2]. With improved detection and medical treatment of stroke, the prevalence of individuals living with such effects of stroke is continually increasing at the national and global scale [2–4]. A major factor associated with long-term disability after stroke is the ability to walk independently [5–8], and is often cited as a goal by individuals with stroke [9, 10]. However, nearly half of individuals with stroke do not regain the ability to walk independently, even after rehabilitation [11, 12]. It is thus important to develop rehabilitation strategies that will promote walking recovery after stroke.

Current best practice guidelines recommend that individuals with stroke should engage in early rehabilitative training that is intensive, repetitive, and task-specific to improve mobility and walking [13, 14]. However, it can be challenging to reach this guideline for individuals with more severe stroke; the amount of walking practice achieved during rehabilitation is especially low for individuals requiring more assistance from their therapist to stand and walk [15]. Electromechanical devices such as body weight-supported treadmills and treadmill-based robotic devices have been proposed to provide walking practice to non-ambulatory individuals during stroke rehabilitation [16, 17], though some research has not supported their use [18, 19]. A possible reason for the mixed findings is the suggestion that treadmill-based assisted gait training does not fully replicate the task-specificity of overground walking [20].

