#### Participants

Consecutive patients with subacute stroke admitted at each rehabilitation hospital will be identified by their treating physiatrists and therapists to be screened for eligibility by a member of the research team. Individuals will be included if they: 1) are within 3 months of stroke onset (ischemic infarct or intracerebral hemorrhage); 2) have one-sided hemiparesis; 3) are 19 years of age or older; 4) are able to understand and follow directions in English; 5) are able to communicate (verbal or physical yes/no indication); 6) are cleared to participate in physical therapy; and 7) require significant assistance (maximal assistance from one or two people) to walk. Individuals will be excluded from the study if they have: 1) a significant musculoskeletal or other neurological condition; 2) cardiovascular contraindications to exercise; 3) co-morbidities that would preclude activity; 4) or pain which is intolerably worsened with exercise. Individuals will also be excluded if they have any contraindications to using the robotic exoskeleton (pregnant, height/weight restrictions). The site coordinator at each hospital with obtain informed consent from potential trial participants.

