#### Sample size estimates

A total of 20 participants will be enrolled in each group (total same *n* = 40). This sample size was calculated using Stata Software (version 11, StataCorp, USA) and assumes a 2-point between-group difference in the Functional Ambulation Category at the end of the intervention [40], setting power at 80% and level of significance at 0.05 (2-sided). This calculation also assumes a standard deviation of 2.0 based on stroke inpatient FAC data from a study by Mehrholz et al. [30]. This between-group difference is realistic, given that participants are 2-person assist (score of 1 on the FAC) on enrolment, and it is expected that those in the Exoskeleton group will make greater improvements in walking ability (independent) compared to those receiving standard care (assistance or supervision required).

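### The 5-Metre and 6-Minute Walk Tests are compared by ANOVA only among participants who recover unassisted walking, a subset selected after randomisation, so a real benefit can be diluted or even change sign

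*Protocol article*

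**What the plan says.** All of this is in the protocol article.

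- **Who is tested.** The footnote to Table 2 (Secondary outcomes) applies to the 5-Metre and 6-Minute Walk Tests after the intervention and at six months: "the outcome will be assessed if the participant is able to walk without physical assistance".
- **How they are analysed.** Statistical analyses: "For measures without a baseline score (i.e., 5-Metre Walk Test, 6-Minute Walk Test), an analysis of variance (ANOVA) will be employed". The same paragraph states an intention-to-treat basis and adds that "any missing data will be assessed and analyzed as appropriate using multiple imputation".
- **Walking status at entry.** Under Participants, those enrolled must "require significant assistance (maximal assistance from one or two people) to walk".
- **Expected effect.** Under Sample size estimates, the Exoskeleton group is expected to "make greater improvements in walking ability (independent) compared to those receiving standard care (assistance or supervision required".
- **The gap is recognised for the primary outcome.** Under Primary outcome, the FAC is preferred to speed and distance measures because "a value is assigned for the FAC even if the participant is not yet independent in walking".

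The article gives no score or rank for speed or distance to a participant who attends but cannot be tested.

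**The concern.** Everyone needs maximal assistance at entry, so whether a participant ever has a walk-test value is decided wholly after randomisation. It is decided by the recovery that the intervention is meant to bring about. An ANOVA on the observed values therefore compares the usual-care participants who recovered walking with the exoskeleton participants who recovered walking. Randomisation does not make those two subsets comparable.

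If the device turns some non-walkers into slow walkers, they enter the exoskeleton mean only, and their counterparts under usual care are left out. The better the device does this, the lower its walkers-only mean. The trial hypothesises greater improvement in walking ability and function, and the Discussion says that the findings will tell clinicians for which outcomes such devices should be used. A diluted or wrong-signed result for speed and endurance would feed into that advice.

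**Working it through.** The article gives no figure for the walk tests, so there is none to reproduce. The check asks how far a walkers-only comparison departs from the effect in all randomised participants.

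**Inputs from the article:** 20 per arm; two-sided 5% level; a FAC difference of 2 points with SD 2.0, that is 2 / 2.0 = 1 SD.

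**Assumptions (not in the article):** the proportions walking, the walking speeds and their SDs.

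**1. Direction.** Let p0 and p1 be the proportions walking unassisted under usual care and exoskeleton. Let A be the mean speed of those who would walk in either arm, d the device's effect on their speed, and B the mean speed of those who walk only because of the device.

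- Walkers-only difference = [p0(A + d) + (p1 - p0)B] / p1 - A
- All-randomised difference with non-walkers at 0 = p0(A + d) + (p1 - p0)B - p0·A
- The walkers-only difference is negative when d < [(p1 - p0) / p0] × (A - B)

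**2. Newly enabled slow walkers.** Take p0 = 0.50 and let the device enable half of the rest, so p1 = 0.75. Take A = 0.60 m/s, B = 0.25 m/s and d = 0.

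- Walkers-only: (0.50 × 0.60 + 0.25 × 0.25) / 0.75 - 0.60 = 0.483 - 0.60 = -0.117 m/s
- All randomised: 0.3625 - 0.300 = +0.0625 m/s
- Break-even: (0.25 / 0.50) × 0.35 = 0.175 m/s. A gain in the other walkers below this still gives a negative walkers-only difference.
- Expected number tested: 20 × 0.50 + 20 × 0.75 = 25 of 40

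Simulation of 4,000 trials per SD gives about -0.11 m/s when speeds are kept positive. A significant difference in the wrong direction occurs in about 34% of trials at SD 0.10 m/s, falling to about 13% at SD 0.30. The rank test on all 40 with zeros rejects in only about 10% to 16%.

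**3. Other assumed values.** With A = 0.80, B = 0.40 and SD 0.25 m/s:

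| Walking, usual care vs exoskeleton | d (m/s) | Walkers-only difference | All-randomised difference | Wrong-direction significance |
|---|---|---|---|---|
| 30% vs 70% | 0 | -0.23 | +0.16 | 31% |
| 40% vs 60% | 0 | -0.13 | +0.08 | 14% |
| 50% vs 80% | 0 | -0.15 | +0.12 | 22% |
| 50% vs 80% | +0.10 | -0.09 | +0.17 | 8% |

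**4. Uniform gain.** Suppose instead that a normal latent walking capacity shifts by 1 SD in everyone, and a participant is tested above a threshold c. The mean among those tested is μ + φ(c - μ) / [1 - Φ(c - μ)]. With 50% of controls walking, c = 0.

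- Usual care: 0.399 / 0.500 = 0.798
- Exoskeleton: 1 + 0.242 / 0.841 = 1.288
- Difference: 0.49 SD, against a true 1 SD

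For control walking rates of 30% to 60% the difference is 0.36 to 0.56 SD. The sign is kept, but power at 20 per arm is about 35% for walkers only, against about 82% for a rank test on all participants with non-walkers at 0.

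**The case against.** The strongest reply is that the protocol chose a primary outcome that avoids this problem. The FAC is scored in everyone, so the main conclusion does not depend on the walk tests. Table 2 also lists the Berg Balance Scale, days to unassisted ambulation and activPAL step counts, none of which carries the walking restriction. A device that makes non-walkers walk would show on the FAC, and a misleading speed result would not be read alone. This stands, and it limits the severity.

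Several stronger readings are tempting but not supported:

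- **That the sign will reverse.** Reversal needs newly enabled walkers to be slower than the others and the others to gain little. The Exoskeleton intervention section makes the second condition plausible, since it says that overground practice is at least as effective once people are ambulatory. Under a uniform gain there is only attenuation.
- **That half the sample will be untested.** The Background says that "nearly half of individuals with stroke do not regain the ability to walk independently, even after rehabilitation". That describes stroke in general and independent walking. The condition here is walking without physical assistance, in people selected for severe limitation. In the scenarios above with half of controls walking, about 25 to 27 of 40 are tested.
- **That non-walkers will have speeds imputed.** Multiple imputation is to be used as appropriate. The article does not say whether untested non-walkers count as missing, so this is an open rule and not a stated plan.
- **That speed and endurance are the leading secondary outcomes.** Table 2 ranks none of them.

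Scoring non-walkers as 0 is also not free of objection. It treats a person who walks with light help as not walking at all, and it partly retests the FAC.

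**Conclusion.** The concern holds for these two secondary outcomes. Both the restricted testing and the ANOVA are stated in the article, and together they give a comparison of subsets selected after randomisation, contrary to the stated intention-to-treat basis. Multiple imputation does not resolve it: left off the untested non-walkers, the comparison stays walkers-only; applied to them, it would assign speeds to people who cannot walk unassisted.

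That the comparison is selected follows from the text alone. The size of the bias does not, because it rests on assumed walking rates, speeds and SDs. Over the ranges tried, it runs from an effect cut to roughly one third to one half of its true size up to a wrong-signed difference. Since the primary FAC result is unaffected, this is a should-fix point.

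**What to change.** Change the analysis wording for the two walk tests:

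1. For the between-group test, give participants who are assessed but cannot walk unassisted 0 m/s and 0 m, or the worst rank.
2. Compare all randomised participants with a rank-based method, stratified by or adjusted for site and Berg Balance Scale stratum, the two randomisation factors.
3. Report the proportion walking unassisted in each arm beside the result.
4. Present walkers-only means as descriptive, and state that the groups so formed are not randomised.
5. Limit multiple imputation to visits that were truly missed.

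No new data are needed, because the FAC is scheduled for every participant at both follow-up visits and shows who cannot walk unassisted. The cost is in interpretation. The result becomes a composite of being able to walk and of speed or distance, and it overlaps with the FAC. It corrects the direction of the comparison but may still have little power: about 10% to 16% in the slow-walker scenario.
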